**Fig. 1 Fig1:**
[figure not shown]
Trial flowchart

### Trial schedule

The trial schedule is outlined in Table 1.

**Table 1 Tab1:** Schedule of participants and investigators

Trial schedule	Day 0	Day 1	Day 2	Day 3	Day 4
Visit to hospital	○				○
Instructions for denture adhesives	○				
Using denture adhesive		○	○	○	○
Eligibility screen	○				
Informed consent	○				
Patients characteristics		○			
Denture satisfaction		○			○
Oral health-related quality life		○			○
Perceived chewing ability		○			○
Perceived swallowing ability					○
Occlusal bite force		○			○
Retentive force		○			○
Masticatory performance		○			○
Oral dryness	○				○
Compliance check					○

#### Day 0

The dentists at each center will ask qualifying complete denture wearers to meet with the coordinator. The coordinator will interview the participants and explain the trial to them. Then, written informed consent will be obtained from each candidate. Once the candidate provides informed consent to the coordinator, an evaluator will perform an eligibility screening to check whether the participant meets any of the exclusion criteria. Next, the coordinator will randomly allocate the qualified candidate to one of the three trial groups using the abovementioned envelope. The participants will be asked to visit the center twice during the study.

#### Day 1

The evaluators will perform the baseline measurements listed in Table 1. The coordinator will describe how to use the denture adhesive to the participant. The participants will be instructed to apply the denture adhesive before eating breakfast, lunch, and dinner, and to remove the remaining denture adhesive immediately before applying new denture adhesive or sleeping at night. The participants will begin applying the denture adhesive before dinner on day 1, and then eat dinner with the denture adhesive applied.

#### Days 2 and 3

The participants will not visit the hospital on these days. However, they will continue to use the denture adhesive three times a day.

#### Day 4

The participants will visit the hospital after eating breakfast with the denture adhesive applied. The appointment will be scheduled so that the participants will have eaten eight meals with the adhesive applied: three breakfasts, two lunches, and three dinners. The final measurements will be performed at the hospital. The participant will give the remaining denture adhesive to the evaluator to check for compliance during the trial.

If the participants feel pain when wearing the dentures and/or have troubles with their existing dentures that require denture adjustment or repair during the trial, the dentists will adequately treat their participants in all of the allocated groups.

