### Randomization, allocation concealment, and sequence generation

A randomized, controlled parallel clinical trial will be conducted at the abovementioned ten centers. Participants will be randomly assigned to one of the following three groups and will be instructed to apply either a denture adhesive or a control solution to both their maxillary and mandibular dentures: cream-type denture adhesive group, powder-type denture adhesive group, and control group (Fig. 1). Balanced allocation of participants to each group will be achieved using the following method: 300 random allocation numbers with no overlap and no underlap will be generated by the “RAND” and “RANK” functions in Excel (Microsoft Japan Co. Ltd., Tokyo, Japan). The first to 300^th^ numbers will be ordered randomly. Then, the first to 100^th^, 101^st^ to 200^th^, and 201^st^ to 300^th^ randomly ordered numbers will be assigned to the cream-type denture adhesive group, powder-type denture adhesive group, and control group, respectively. As per the assignment, 300 envelopes containing a card stamped with the group name will be prepared. The 300 envelopes will be divided 30 by 30 for ten centers in sequence, which means that each of the ten centers will receive 30 envelopes. Then, the coordinator at each center will open one envelope and allocate a qualifying participant to the indicated group after the patient agrees to participate in the study and provides informed consent. This method enables us to allocate the 300 numbers to the three groups equally and randomly. Once the 300 participants have been completely allocated, the number of participants in each of the three groups will be equal. Blinding the participants to the intervention is not feasible, since the participants will be able to determine the type of denture adhesive they are using during application. Evaluators are blinded to the allocation.

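### Participants are allocated on day 0 but the self-rated primary outcome gets its baseline on day 1; nothing withholds the arm in between, and Table 1 and the text disagree on instruction and visit days

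*Protocol article*

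**What the plan says.** The Trial schedule section sets out day 0 as consent, then the eligibility screen, then allocation: "Next, the coordinator will randomly allocate the qualified candidate to one of the three trial groups using the abovementioned envelope". The randomization section agrees: "the coordinator at each center will open one envelope and allocate a qualifying participant to the indicated group". Under day 1 the article says: "The evaluators will perform the baseline measurements listed in Table 1". Table 1 marks denture satisfaction, oral health-related quality of life, perceived chewing ability, bite force, retentive force and masticatory performance in the day 1 column. Oral dryness is the exception, with its first measurement on day 0.

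On blinding, the randomization section says: "Blinding the participants to the intervention is not feasible, since the participants will be able to determine the type of denture adhesive they are using". The reason given concerns the moment the product is applied. Evaluators are blinded.

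Two items in the schedule conflict:

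- **Instruction.** The Table 1 row "Instructions for denture adhesives" is marked on day 0. The text describes the instruction under day 1, after the sentence on baseline measurement.
- **Visits.** Table 1 marks hospital visits on days 0 and 4 only, and the text says: "The participants will be asked to visit the center twice during the study". Yet day 1 includes measurements with an occlusal force meter and a colorimeter.

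**The concern.** Baseline values are protected from the effect of allocation only if they are taken before allocation, or while the participant does not know the arm. Here the written order is allocation first, and no safeguard is stated. The primary outcome is the participant's own mark on a 100-mm scale, so evaluator blinding does not protect it. Someone who knows that saline, or an adhesive, is coming could rate the existing denture differently before using anything.

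The baseline matters because the null hypothesis in the Background has two parts: no difference in outcomes, and no difference in improvement from baseline to day 4. The Statistical analysis section also plans paired pre/post tests. A baseline shifted by knowledge of the arm enters the improvement part and the paired tests directly. The two schedule conflicts decide whether this can happen, so they are more than editorial slips.

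**Working it through.** **Order of events.** The documents allow two sequences.

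1. *Table 1 followed.* Day 0: consent, eligibility, envelope, instruction. Day 1: baseline, then first application before dinner. The instructions differ by product (cream in strips or dots, powder shaken on, saline from eight single-use bottles), so the participant knows the arm at baseline.
2. *Day 1 text followed.* Day 0: consent, eligibility, envelope opened by the coordinator. Day 1: baseline, then instruction, then first application. The participant could rate baseline without knowing the arm, provided nobody tells them on day 0. No sentence says so.

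If days 0 and 1 are really one attendance, which would fit two visits, the written order is still allocation and then baseline.

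**How a shift enters each analysis.** Let b be the between-arm difference at baseline caused by knowing the arm, with no effect on day-4 values.

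- Contrast of change scores: bias of size b, opposite in sign to the shift.
- Paired pre/post test within an arm: that arm's mean change is biased by the full shift in that arm.
- Contrast of day-4 values only: bias 0.
- Baseline-adjusted contrast, if one were used: about slope × b. The article specifies none, and its listed covariates do not include baseline satisfaction.

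**Scale.** The Sample size section gives a 29 mm meaningful difference and spreads of 20 and 23 mm, called variances. Read as standard deviations (an assumption), they pool to √((20² + 23²)/2) = 21.55 mm. The article's 100 per group does not reproduce from these inputs: 2 × (1.960 + 0.842)² × 21.55² / 29² = 8.7, so 9 per group, or 10 after 10% dropout. That is a separate matter and this point does not depend on it. With 90 evaluable per arm, the difference detectable at 80% power and two-sided 5% is 2.802 × 21.55 × √(2/90) = 9.0 mm.

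The documents give no value for b. For an assumed 3 to 5 mm:

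- against 29 mm: 3/29 = 10% to 5/29 = 17%;
- against 9.0 mm: 3/9.0 = 33% to 5/9.0 = 56%.

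**False-positive rate of a change-score comparison.** Assumptions: no true effect, 90 per arm, SD 21.55 mm at both times, normal approximation, pre/post correlation r from 0.3 to 0.7 (not in the documents). The standard error is 21.55 × √(2(1 − r)) × √(2/90). At r = 0.5 it is 3.21 mm.

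| Assumed b | r = 0.3 | r = 0.5 | r = 0.7 |
|---|---|---|---|
| 0 mm | 5% | 5% | 5% |
| 2 mm | 8.2% | 9.5% | 12.7% |
| 5 mm | 26.0% | 34.3% | 52.0% |

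A baseline comparison between two arms has the same 9.0 mm detectable difference, so the data could not reliably show a shift of 2 to 5 mm afterwards.

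**The case against.** The strongest reply is that early knowledge of the arm is inferred. The coordinator opens the envelope, and nothing says the participant is told on day 0. The day 1 text puts baseline before instruction, and the randomization section ties recognition to application, which first happens before dinner on day 1. This stands: only the Table 1 instruction mark points to knowledge at baseline, and it is one side of an unresolved contradiction. What remains is that the article withholds the arm nowhere and its own table discloses it too early.

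Other parts of the reply also stand:

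- The Statistical analysis section does not say whether the analysis of variance uses day-4 values or change. If it uses day-4 values, that comparison is unaffected.
- Evaluators are blinded and several outcomes are read from instruments. Exposure lies mainly in the self-ratings and, to a lesser degree, in bites that depend on effort.
- The direction is unknown. Disappointed saline participants who rate low at baseline would enlarge their own improvement and dilute the adhesive effect.
- A shift of 3 to 5 mm is small against 29 mm. However, the article judges significance at p < 0.05 and allows early stopping for significant benefit, so a bias well below 29 mm can still change a conclusion.

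A reader might also infer that withdrawals between allocation and day 1 undermine the intention-to-treat analysis. The documents do not show this. Days 0 and 1 may be one attendance, a person who leaves that early would usually lack a day-4 value too, and the article says strategies for missing data will be considered.

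**Conclusion.** The point holds as a weakness in the written order of events together with two contradictions in the schedule. Allocation precedes the baseline of the self-rated primary outcome and of nearly all other outcomes, participants are unblinded, and no safeguard is stated. If Table 1 is followed, participants rate baseline knowing their arm. Any shift would pass one for one into change-from-baseline and pre/post results for self-rated and effort-dependent outcomes.

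The documents do not support reading this as proof that baselines are biased, or that the between-group result is invalid. Knowledge of the arm at baseline is one of two readings, a day-4-only comparison does not use the baseline, and the size and direction of any shift are unknown. The percentages above rest on assumed shifts, assumed correlations and the reading of the stated variances as standard deviations. This is a should-fix matter.

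**What to change.** For participants still to be enrolled, complete consent, eligibility and all baseline measures before the envelope is opened, then give the instructions. Correct the article so that Table 1 and the text agree on the day of instruction and on which days participants attend. If days 0 and 1 are one visit, say so.

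For participants already enrolled, document the order actually used at each center, including whether the arm was known before baseline. If it was withheld, stating that settles the matter for them. Otherwise, base the between-group conclusion for these participants on day-4 values, at least as a sensitivity analysis beside any change-score result.

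No measurement is added and the sample size does not change. The costs are a longer visit before allocation, a few baselines on people who are then not randomised, and two baseline regimes within one ongoing trial. The last should be recorded for each participant so that results can be shown by regime.

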### Intervention

The intervention in this trial is the use of one of the following denture adhesives or control solution on the maxillary and mandibular complete dentures for four consecutive days: cream-type denture adhesive consisting of methoxyethylene/maleic anhydride copolymer, petrolatum, sodium carboxymethyl cellulose, liquid paraffin, and propyl parahydroxybenzoate (Polygrip S, GlaxoSmithKline, Tokyo, Japan); powder-type denture adhesive consisting of methoxyethylene/maleic anhydride copolymer, and sodium carboxymethyl cellulose (Polygrip powder, GlaxoSmithKline, Tokyo, Japan); or control consisting of saline solution (Isotonic Sodium Chloride Solution 20 mL CMX; Chemix Inc., Yokohama, Japan).

As mentioned above, the coordinator will instruct the participants on how to use the denture adhesive or control. The procedures for applying the powder-type denture adhesive are as follows: (1) before applying the powder, dentures should be cleaned, rinsed, and left wet; (2) gently squeeze or tap the bottle to dispense the powder onto the entire denture surface; and (3) shake off any excess powder, press the dentures into place, and hold briefly. The instructions for applying the cream-type denture adhesive are as follows: (1) before applying the cream, dentures should be cleaned, rinsed, and dried; (2) gently squeeze the tube and place the cream in small strips or a series of dots on the denture surface; and (3) press dentures firmly in place and hold briefly. Finally, the procedures for applying the control (distributed as eight bottles, with one bottle to be used per application) are as follows: (1) before applying the solution, dentures should be cleaned, rinsed, and left wet; (2) gently squeeze the bottle to dispense the liquid onto the entire denture surface; (3) press the dentures into place, and hold briefly. Compliance with the intervention with regard to using the denture adhesives and control will be checked by weighing the remaining denture adhesives and counting the remaining number of saline solution bottles, respectively.

### Primary outcome measures

Experts and members of the Japan Denture Care Society selected the outcomes for the current trial after reviewing previously published articles on denture adhesives. The primary outcome is a general satisfaction rating obtained with a 100-mm VAS. The satisfaction ratings will be determined using valid questionnaires with eight evaluation items: general satisfaction, ability to speak, ease of cleaning, stability, retention, comfort, and esthetics [24]. The participants will be asked to assess their current existing complete dentures and to record their satisfaction rating for each item on the questionnaire by drawing a vertical line on a 100-mm VAS. Each vertical line in the questionnaire represents “very satisfied” (100) at the extreme right and “very dissatisfied” (0) at the extreme left. Data will be recorded as continuous variables at 1-mm intervals using calipers, beginning at the extreme left. The general satisfaction will be measured twice: at baseline and day 4.

### Secondary outcome measures

The secondary outcomes will be measured twice: at baseline and day 4.

#### Occlusal bite force

The occlusal bite force [16, 17, 25] will be measured bilaterally at the first molar region using a force transducer occlusal force meter (GM10; Nagano Keiki, Tokyo, Japan) consisting of a digital hydraulic pressure gauge and a vinyl biting element covered with a plastic sheath. A pressure gauge displays the bite force values in Newtons on a digital screen.

#### Resistance to dislodgement

The resistance to dislodgement, which is defined as the maximum occlusal force exerted during a bite before the denture dislocates, will be measured by placing the abovementioned occlusal force meter at the incisor and canine regions. Moreover, the resistance to dislodgement quantitatively assesses the bite force needed to dislodge maxillary and/or mandibular dentures. It also demonstrates the benefits of using denture adhesive to improve the retention and stability of the tested dentures.

#### Masticatory performance

The masticatory performance, or mixing ability, will be evaluated using color-changeable chewing gum (Masticatory Performance Evaluating Gum; XYLITOL Lotte Co., Ltd., Tokyo, Japan) and a colorimeter (CR-13; Konica-Minolta Sensing, Tokyo, Japan). As per previous reports [26, 27], the measurements will be performed as follows: (1) participants will be instructed to chew the gum depending on their preferred side, without any instructions as to the chewing side, for 60 chewing cycles at a rhythm of once per second, which will be set with a metronome; (2) the chewed gum will be extracted immediately after chewing, flattened to a thickness of 1.5 mm by compressing the gum between two glass plates, and then placed on polyethylene films; and (3) the color will be measured through the polyethylene films using a colorimeter.

#### Oral health-related quality of life

The OHR-QoL will be measured with the Japanese version of the Oral Health Impact Profile for edentulous patients (OHIP-EDENT-J). The OHIP-EDENT-J is composed of 19 items distributed among the following seven subscales: functional limitations, pain, psychological discomfort, physical disability, psychological disability, social disability, and handicap [28]. Participants will be asked to rate the frequency with which they believe they encountered these items on a 5-point Likert scale, as follows: never (score 0), hardly ever (score 1), occasionally (score 2), fairly often (score 3), and very often (score 4). The sum of the ratings for all 19 items will be used as a score of OHR-QoL impairment, with the lowest score being 0 and the highest score being 76. The more the score increases, the more the OHR-QoL decreases.

#### Perceived chewing abilities

The trial will utilize two types of questionnaires to measure the patients’ self-reported chewing abilities. One of the questionnaires will measure the participants’ general perception of their chewing abilities during the mastication of each food (see list below), defined as the perceived chewing ability. The other questionnaire will measure chewing perception by asking how well the participants believe they chewed their food immediately before swallowing, defined as the perceived chewing ability at swallowing. Using the 100-mm VAS, participants will evaluate their perceived chewing ability and perceived chewing ability at swallowing when consuming the following foods: soybean curd, fish sausage, soybean sprout, cubic rice cracker, and dry squid. Each vertical line on the VAS for chewing represents “very easy to chew” (100) at the extreme right and “very difficult to chew” (0) at the extreme left, while the lines on the VAS for perceived chewing ability at swallowing represent “swallowed without chewing” at the extreme right (100) and “swallowed with chewing” (0) at the extreme left. Data will be recorded as continuous variables by measuring the distance at 1-mm intervals using calipers, beginning at the extreme left.

### Adverse events

The adverse events reported by participants are recorded on an as-needed basis.

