### Interim analyses and early stopping of the clinical trial

The data and safety of the clinical trial will be monitored. Interim analyses of the trial will be performed when 100 and 200 participants have completed the trial. The trial will be stopped under the following conditions: (1) excess harm is observed, (2) statistically significant benefits are observed, (3) little additional useful information or negligible chance of demonstrating efficacy will be yielded if fully completed. These early stopping rules will help minimize harm and maximize the benefits for the patients enrolled in the RCT.

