## Discussion

Japan, in the midst of an aging society, has many disabled denture wearers who cannot visit a dental office even though their poor denture quality is decreasing their quality of life. Denture adhesives could help some of these patients. However, Japanese dentists hesitate to recommend or apply denture adhesives to their patients, as no Japanese guidelines for denture adhesives exist. This RCT will provide evidence of the effects of denture adhesives to complete denture wearers, caretakers at nursing homes, prosthodontic educators, and dentists in Japan. Moreover, the evidence generated by this trial in Japan will help to establish evidenced-based denture adhesive guidelines in Japan. These guidelines will release Japanese dentists from the dogma that denture adhesives do more harm than good. Furthermore, we believe the new evidence concerning the use of denture adhesives from Japan will aid dentists in their daily practice even in other countries.

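### Adverse events are recorded only as unscheduled participant reports in an unblinded trial, a weak basis for the excess-harm stopping condition

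*Protocol article*

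**What the plan says.** The Adverse events section of the protocol article is a single sentence: "The adverse events reported by participants are recorded on an as-needed basis". It names a source (the participant) and a timing (as needed). It names no question, form, examination or visit.

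Other parts of the article bear on this:

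- **Table 1 (Trial schedule)** has a row for each questionnaire and measurement, for oral dryness and for the compliance check. It has none for adverse events. Participants do not attend on Days 2 and 3.
- **Participant characteristics** lists oral mucosa condition among items collected at baseline. No examination of the mucosa after use is described.
- **Trial schedule**, closing paragraph: pain or denture trouble is to be treated in every group. Whether it is then logged as an adverse event is not stated.
- **Interim analyses and early stopping**: "The data and safety of the clinical trial will be monitored". Also, "Interim analyses of the trial will be performed when 100 and 200 participants have completed the trial". The first stopping condition is that "excess harm is observed". No event type, comparator, threshold or data source is given.
- **Randomization**: "Blinding the participants to the intervention is not feasible", while "Evaluators are blinded to the allocation".
- **Outcome sections**: the OHIP-EDENT-J, with its pain subscale, and the satisfaction questionnaire, with its comfort item, are given to all participants at baseline and Day 4.

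**The concern.** A stopping condition framed as an excess is most naturally read as a comparison between adhesive and saline users. That comparison is sound only if events are sought in the same way, from everyone, in every group. The described method leaves recording to whatever participants report, at no set time.

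Two problems could follow. Events may be missed in all groups, so that a real excess is harder to see. Or participants who know they are using an adhesive may report more, or less, than those using saline, so that the groups differ for reasons unrelated to true event rates. In either case, those reviewing the interim data could not tell a low or unequal count from an artefact of recording. A low count might later be taken as evidence of safety.

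**Working it through.** The article gives no adverse event rate, harm margin or power for harm, so there is no figure to reproduce. The main check is a comparison of texts. The arithmetic after it only shows scale, and every event rate and capture fraction in it is an assumption.

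**1. Texts side by side**

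| What the harm condition needs | What the article describes |
|---|---|
| A defined source of event counts | Participant reports, as needed |
| The same enquiry in each group | No scheduled enquiry in Table 1 |
| Reporting not influenced by knowledge of product | Participants not blinded |
| Observation after use | Mucosal condition at baseline only; pain subscale and comfort item at Day 4, not linked to the rule |
| A denominator | Known: 100 allocated per group |

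Only the denominator is secured. Whether the numerator is complete and comparable is left open.

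**2. Equal under-capture in both groups**

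Inputs: 100 per group (Sample size calculation). At the interim looks, 100/3 ≈ 33 and 200/3 ≈ 67 per group if groups fill evenly (assumption). Assumed true risks are 12% and 2%. With capture fraction s, the observed risks are 0.12s and 0.02s. Power is the sum of the binomial probabilities of all pairs of counts that give p ≤ 0.05 on a two-sided Fisher exact test.

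| Per group | s = 1.0 | s = 0.7 | s = 0.5 | s = 0.3 |
|---|---|---|---|---|
| 100 | 76% | 53% | 31% | 9% |
| 67 | 50% | 28% | 13% | 2% |
| 33 | 12% | 4% | 1% | <1% |

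At the first look the expected counts are 33 × 0.12 ≈ 4.0 against 33 × 0.02 ≈ 0.7 even with full capture. Sample size therefore already limits detection there, and under-capture makes it worse.

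**3. Unequal capture with no true difference**

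Assume a true risk of 10% in both groups, with 80% of events captured in one and 40% in the other. Expected counts per 100 are 100 × 0.10 × 0.8 = 8 and 100 × 0.10 × 0.4 = 4, an apparent doubling.

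Under the normal approximation, the chance of a significant difference at two-sided 5% is Φ[(d − 1.96·SE₀)/SE₁]:

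- d = 0.08 − 0.04 = 0.04
- SE₀ = √(0.06 × 0.94 × 2/100) = 0.0336
- SE₁ = √(0.08 × 0.92/100 + 0.04 × 0.96/100) = 0.0335
- Φ[(0.04 − 0.0658)/0.0335] = Φ(−0.77) ≈ 22%

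For true risks of 5% and 20% the same formula gives about 13% and 41%. Fisher's exact test is more conservative: about 4%, 14% and 34% for true risks of 5%, 10% and 20%. Either way, the apparent risk ratio of 2 is an artefact of recording.

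**4. Reading a zero count**

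With no events in 100 participants, the one-sided 95% upper limit for the recorded risk is 1 − 0.05^(1/100) = 3.0%. If only half of events are captured, the corresponding limit for the true risk is about 0.0295/0.5 = 5.9%.

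**The case against.** The best defence is that this is a condensed article. Forms, elicitation wording and safety procedures usually sit in a full protocol, and the article does say that safety will be monitored. That has weight as regards detail. It does not remove the point, because the article is not silent: it states a method, and Table 1 lists the other assessments without this one.

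A reader might infer more than the text supports:

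- **That events count only if volunteered.** A participant asked at Day 4 also reports an event, so the sentence does not rule out solicitation.
- **That the counts are biased by group.** Lack of blinding makes this possible. No document shows it.
- **That no rate per group can be formed.** The denominators follow from the allocation. Only the numerators are in doubt.
- **That harm against benefit is a trial question.** The stated aim is efficacy. The hope that guidelines will "release Japanese dentists from the dogma that denture adhesives do more harm than good" is a Discussion remark about later guidelines.
- **That harm information is wholly passive.** Pain and comfort are asked of everyone at both time points, and oral dryness is measured at Day 0 and Day 4. However, the pain and comfort answers are also unblinded self-reports, none of these measures records events, and none is tied to the stopping condition.

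The power figures can also be challenged: the rates are assumed, the article specifies no test for harm, and at the first look power is low even with perfect recording. All of that stands, which is why the figures serve only to show scale.

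**Conclusion.** The point holds as a weakness of the stated method. As written, the excess-harm condition would rest on unstructured participant reports in an unblinded trial, with nothing to ensure that they are complete or comparable between groups. It needs only the Adverse events sentence, Table 1, the blinding statement and the stopping condition, together with the reading that an excess means a comparison between groups.

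Its size cannot be estimated from the documents. Under the assumed risks of 12% and 2%, halving capture lowers power from 76% to 31% at 100 per group, and from 50% to 13% at about 67 per group. Other rates would give other figures.

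The change is worth making but is not critical: use lasts four days and the primary efficacy analysis is unaffected.

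**What to change.** At the existing Day 4 visit, have the coordinator ask every participant in all three groups the same scripted open question, followed by a short fixed checklist of oral complaints. The coordinator should do this, not the evaluator, because the answers could reveal the product to someone who is meant to be blinded.

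Then:

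- Add an adverse event row to Table 1.
- Report numbers and rates by group, with the number asked as denominator.
- Name these counts, alongside the pain and comfort data already collected, as the input to the excess-harm review.
- Because recruitment is under way, report participants enrolled before the change separately.

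The cost is a short form and a minute or two per participant at a visit that already takes place. The downside is that more minor complaints will be recorded and must be reported.

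If events are already solicited uniformly at Day 4, a sentence in the Adverse events section and a row in Table 1 saying so would settle the collection question. The data that feed the harm review should still be named.
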